### Data Monitoring

Monitoring visits will be conducted by representatives of NuBiyota LLC according to the ICH guidelines for good clinical practice (GCP; E6). All information obtained during the course of this study is strictly confidential, and each subject’s anonymity will be protected at all times. The investigator grants permission to NuBiyota LLC (or designee) and appropriate regulatory authorities to conduct on-site monitoring and/or auditing of all appropriate study documentation. Subjects will be identified by a study number and will not be identified in any publication or reports. The information collected for the study will be kept in a locked and secure area by the study doctor for 25 years. Only the study team, the representatives of the Research Ethics Board, and the representatives of Health Canada will have access to the data.

In addition, the study data may be transferred to the people or groups listed above to be processed for the purposes of the study, for product registration purposes and scientific purposes in general, ensuring compliance with laws and regulations. Any study data transferred outside of this study site will not include the name, address, or health insurance number of the subject. Instead, the study data will be coded to ensure that each subject’s identity is kept confidential.

### Adverse Events

The frequencies and severity of AEs will be collected on a questionnaire from the first day of the assigned study treatment through 14 days following the last assigned study treatment. AEs will be assessed and recorded at all in-hospital visits and phone calls; they will be categorized by frequency, severity, and causality.

#### Severity

To rate the severity of AEs, the following 4-point rating scale will be used:

Life-threatening (4 points): The subject is at risk of death due to adverse experiences as it occurred. This does not refer to an experience that hypothetically might have caused death if it was more severe.Severe (3 points): Signs or symptoms result in a complete inability to pursue regular activities.Moderate (2 points): Signs or symptoms disrupt regular activities.Mild (1 point): Signs or symptoms present but do not disrupt regular activities.

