#### Secondary Objectives

The secondary objectives are to assess changes in metabolic functioning/levels before, during, and after treatment; to assess safety and tolerability, including adverse events (AEs) with a severity of grade 2 or above; and to assess potential correlation between early life stress (childhood emotional/physical/sexual abuse history, etc) and changes in MDD biomarkers as well as response to treatment.

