### Discontinuation Criteria

A participant may be discontinued from treatment or withdrawn from the study at any time if the participant, the principal investigator, or the investigational product sponsor does not feel that it is not in the participant’s best interest to continue. The following is a list of possible reasons for treatment discontinuation:

Participant’s withdrawal of consentAn AE that in the opinion of the investigator would be in the best interest of the participant to discontinue the study treatmentProtocol violation requiring discontinuation of the study treatmentLost to follow-upRequest by NuBiyota LLC for early termination of the studyNewly pregnant participants.

If a participant is withdrawn from treatment due to an AE, the participant will be followed up and treated by the investigator until the abnormal parameter or symptom has resolved or stabilized. All participants are free to withdraw from participation at any time, for any reason, specified or unspecified, and without prejudice. Reasonable attempts will be made by the investigator to provide a reason for the withdrawal of participants. No further data will be collected once a participant has been withdrawn.

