### Molecular Analysis

Blood samples will be taken at screening, *w*eek 4, and *w*eek 8 and sent to Core Laboratories at Kingston Health Sciences Centre, Kingston General Hospital to analyze changes in cortisol levels, liver function, lipids, inflammatory markers (cytokines IL-10 and IL-6, TNF-α, TGF-β, and C-reactive protein), neurotransmitters (5-HT, *DA*, and *NE*), and immunoglobulins (IgA, IgG, and IgM). Baseline levels of creatinine, electrolytes, thyroid-stimulating hormone, complete blood count, and glucose will be taken only at screening to ensure that it is safe for participants to consume the investigational product at baseline. Fecal samples will be collected at all in-hospital visits. The participants will be provided with a stool kit and a Styrofoam case, with instructions at each visit. Upon collecting the sample from the participants, it will be stored at –62°C. Throughout the study, the samples will be sent to the University of Guelph for 16s RNA gene sequencing to determine the gut microbiome composition before, during, and after treatment.

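### A symptom-free laboratory abnormality short of risk of death can score at most 1 on the adverse-event severity scale, so the count of events of grade 2 or above misses it

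*Protocol article*

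**What the plan says.** The relevant text sits in several sections of the protocol article.

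- **Secondary Objectives.** One objective is "to assess safety and tolerability, including adverse events (AEs) with a severity of grade 2 or above". Another, in the same sentence, covers changes in metabolic levels and carries no severity threshold.
- **Severity.** The scale is introduced with "To rate the severity of AEs, the following 4-point rating scale will be used". Its three lower steps are "Mild (1 point): Signs or symptoms present but do not disrupt regular activities", "Moderate (2 points): Signs or symptoms disrupt regular activities" and "Severe (3 points): Signs or symptoms result in a complete inability to pursue regular activities". The top step, four points, requires that the subject was at risk of death when the event happened, and refers to neither symptoms nor activities. No laboratory criterion appears at any step.
- **Molecular Analysis.** Blood drawn at screening, week 4 and week 8 is used to "analyze changes in cortisol levels, liver function, lipids, inflammatory markers", as well as neurotransmitters and immunoglobulins. Creatinine, electrolytes, thyroid-stimulating hormone, blood count and glucose are tested at screening only.
- **Discontinuation Criteria and Causality.** For a participant withdrawn from treatment because of an adverse event, "the participant will be followed up and treated by the investigator until the abnormal parameter or symptom has resolved or stabilized". The Causality section says nearly the same, and names clinically relevant abnormalities found by the investigator as one source of adverse events.
- **Safety and Tolerability.** Product safety is judged from recorded symptoms and adverse events. All adverse events are recorded by frequency, severity and causality.

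**The concern.** The protocol lets a laboratory abnormality be an adverse event, and it repeats blood tests on treatment. The only severity scale it gives separates mild, moderate and severe by the effect on daily activities. A laboratory value has no direct effect on activities, so the scale cannot rank one abnormality above another until life is at risk. The safety objective then highlights events from the second step of that scale upward.

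What is at stake is how a grade 2 or above table can be read. In a small phase 1 study of a live 40-strain product, such a table could look clean although a participant had a marked liver-enzyme rise without feeling ill. A reader who sees only that table would not know that it could not show such an event.

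**Working it through.** No sample size, power or error rate is involved, and the plan states no figure to reproduce. The check takes one type of record, a laboratory abnormality without symptoms that has been recorded as an adverse event, and tests it against each step in the Severity section.

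| Points | What the step requires | Can the record meet it? |
|---|---|---|
| 1 | A sign or symptom, activities undisturbed | Yes, if a laboratory finding counts as a sign |
| 2 | Activities disrupted | No |
| 3 | Complete inability to carry on activities | No |
| 4 | Risk of death as the event occurred | Only if the abnormality itself threatens life at that time |

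The possible scores are therefore 1 or 4, never 2 or 3. If a laboratory finding is not a sign, the record does not fit step 1 either and has no grade. In both cases it stays below the threshold unless life is at risk.

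Three example records, graded literally:

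1. Liver enzymes far above the reference range at week 4, participant feels well, life not at risk: 1 point, not counted at grade 2 or above.
2. Marked rise in C-reactive protein at week 8, no symptoms, life not at risk: 1 point, not counted.
3. Bloating that disrupts a day's activities: 2 points, counted.

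Size. The Results section reports 21 participants enrolled, of whom 12 completed with at least one visit after baseline. One participant moved across the threshold changes the participant rate by

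- 1/12 = 0.083, or 8.3 percentage points, with 12 as denominator;
- 1/21 = 0.048, or 4.8 percentage points, with 21 as denominator.

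These figures show the weight of a single event. They do not estimate an effect, because the article gives no rate of laboratory abnormalities and names no safety analysis set.

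**The case against.** A reader might infer something stronger: that severity rests on activity disruption alone, that a symptom-free abnormality stays at grade 1 however large it is, and that it drops out of the safety objective. The document does not support this, for four reasons.

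- Four points are defined by risk of death, without reference to symptoms or activities. An abnormality that threatens life scores 4 and is counted.
- The objective presents events of grade 2 or above as something it includes, so the threshold is one component and not a filter. All adverse events are recorded, and no section makes a grade 2 or above table the only safety summary.
- The protections for participants do not depend on the grade. Discontinuation for an adverse event rests on the investigator's judgement. Serious-event status and expedited reporting rest on seriousness, expectedness and relatedness.
- Laboratory changes are analysed under their own secondary objective. The article attaches an explicit safety purpose only to the tests done at screening alone, so it would go too far to call the week 4 and week 8 panel the trial's only objective safety signal.

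All four stand, and they confine the point to the grade 2 or above count.

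It can also be said that an activity-based scale is a legitimate choice, and that a laboratory toxicity table is detail an article may leave to the full protocol. This carries less weight. The article does not leave grading open: it states the scale that will be used for adverse events, and the result for laboratory events follows from that rule. Nor does the metabolic objective fill the gap, because it concerns changes in levels and does not grade an individual's abnormality.

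Finally, analysis was already under way when the article was written, so a grading rule fixed in advance may no longer be possible. That is correct, and the change must be labelled accordingly.

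**Conclusion.** The point holds as a narrow reporting weakness. An asymptomatic laboratory abnormality that is recorded as an adverse event and falls short of risk of death scores at most 1, and so is left out of the count of events of grade 2 or above. It is not lost from the trial's records, and its handling as a possible serious event is unaffected.

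The conclusion rests on two assumptions. First, the grade in the Secondary Objectives means the points in the Severity section; the article does not say so, but it gives no other severity scale. Second, the abnormality has been recorded as an adverse event, which depends on the investigator finding it clinically relevant.

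The number of events affected is unknown and may be zero. The correction is worth making because it is cheap and because, in a trial of this size, one event visibly changes the rate.

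**What to change.** In the Severity section, keep the activity-based scale for symptomatic events. Add that laboratory adverse events are graded by their deviation from the laboratory's reference range, using a named standard laboratory toxicity table. Apply this to the values already collected at weeks 4 and 8 that such a table covers, for example liver function and lipids. State which measured markers it does not cover, so that readers know those have no laboratory grade.

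State in the Secondary Objectives that the summary of events of grade 2 or above uses this grade for laboratory events, and that grade means the points on the severity scale for all others. List every serious adverse event with that summary, whatever its activity-based grade.

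Date the change, and label it post hoc if any results had been seen by then.

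The cost is some regrading work and a grade 2 or above count that may rise. No new samples or visits are needed, and no rule on dosing, discontinuation or treatment changes.

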#### Causality

To gauge the causal relationship of the AEs to the treatment, the following 4-point scale will be used:

Probable (4 points): A clear-cut temporal association with improvement on cessation of investigational medicinal products or reduction in dose. Reappears upon rechallenge.Possible (3 points): Follows a reasonable temporal sequence from administration. May have been produced by the subject’s clinical state, environmental factors, or other therapies administered.Unlikely (2 points): Does not follow a reasonable temporal sequence from administration. May have been produced by environmental factors or other therapies administered.Unrelated (1 point): Due only to extraneous causes and does not meet the criteria listed under unlikely, possible, or probable.

The investigator will probe, via discussion with the participant, for the occurrence of AEs during each patient visit and record the information in the site’s source documents. AEs will be recorded in the participant case report form. AEs will be described by duration (start and stop dates and times), severity, outcome, treatment, and relation to the study drug or, if unrelated, the cause.

AEs will be collected in the following ways: (1)any symptoms or events self-reported spontaneously by the patient,

(2) the patient will be asked open-ended questions to answer about their health (eg, “How are you feeling since we saw you last in clinic?”), and (3) any clinically relevant abnormalities noted by the investigator during follow-up interviews.

In the event of a reported AE, if the principal investigator decides that it would be in the best interest of the participant to discontinue treatment, the participant will be removed from the study. If a participant is withdrawn from treatment due to an AE, the participant will be followed and treated by the investigator until the abnormal parameter or symptom has resolved or stabilized.

Once withdrawn, if participants choose to withdraw the biological samples they provided before the AE, they are able to do so, and we will ensure that the samples are destroyed. If tests have already been performed on the sample(s), it will not be possible to withdraw those results. However, no further testing will be performed. The samples that have already been tested will continue to the analysis portion of the study. 

### Serious Adverse Events

Serious adverse events (SAEs) will also be reported to the HSREB and given immediate care. SAEs are any untoward medical occurrence that at any does results in death, is life-threatening, requires inpatient hospitalization or prolongation of existing hospitalization, results in persistent or significant disability/incapacity, or is a congenital anomaly/birth defect. 

### Requirement to Report

AEs that are considered serious, unexpected, and possibly or probably related to the study drug are subject to expedited reporting to the REB and Health Canada in accordance with C.05.014 of the Canadian Food and Drug Regulations. It is the responsibility of the investigator to report serious, unexpected, and possibly or probably related AEs to the REB. It is the responsibility of NuBiyota LLC to report serious, unexpected, and possibly or probably related AEs to Health Canada. 

### Reporting Procedures

After learning that a participant has experienced an SAE, the investigator or designee is responsible for reporting the SAE to the medical monitor, regardless of relationship or expectedness, within 24 hours of becoming aware of the event.

This report may be accomplished by completing an SAE form, which will include the following:

Subject’s study numberSubject’s genderDate of first dose of investigational drug(s)Date of last dose of investigational drug(s), if applicableAE termTime and date of occurrence of the eventA brief description of the event, outcome to date, and any actions takenThe seriousness criteria (on) that were metConcomitant medication at the onset of the eventRelevant medical history informationRelevant laboratory test findingsInvestigator’s opinion of the relationship to investigational drug(s) (“Is there a reasonable possibility that the investigational drug caused the SAE? Yes or No?”).

### Approvals and Registration

This trial will be conducted in compliance with the protocol, GCP, and the applicable local regulatory requirements and laws. Ethics approval was obtained from Queen’s University HSREB (protocol number 6025187) on March 28, 2019. A no-objection letter from Health Canada was obtained for the use of MET-2, in accordance with part C, division 5 of the Food and Drug Regulations. The trial was registered on ClinicalTrials.gov on August 9, 2019 (NCT04052451), and is being funded by NuBiyota LLC and MITACS.

If any changes are made to the study protocol by the investigator, such as changes to eligibility criteria, informed consent, outcomes, and/or analyses, they will be communicated to the sponsor, the HSREB, Health Canada, and trial registry. If required, all participants will be informed and consented once again.

### Access to Data

The investigator and team will have access to the final trial dataset. This has been outlined in a clinical trial agreement and has been agreed upon by both the investigator and the sponsor. Upon completion of trial and data analysis, the study results will be published for participants, health care professionals, the public, and all other relevant groups to access. The publications will be written and authored by the principal investigator and team.

## Results

The study received approval from the Queen’s University Health Sciences and Affiliated Teaching Hospital Research Ethics Board on March 28, 2019. Participant recruitment began in May 2019. As of March 2020, we have enrolled 21 participants, of which 12 participants completed the study with at least one visit postbaseline. We have completed recruitment for this study and are currently in the process of analyzing data. We expect to see improvement in depressive and anxiety symptom scores from baseline to week 10, to be mediated by a decrease in pro-inflammatory markers and an increase in anti-inflammatory markers. Furthermore, we hope to see lasting changes in the microbiome composition reflecting a similar composition to that of the donor by the end of the study.

## Discussion

Currently, there are many different psychological and pharmacological treatments that target symptoms of depression and anxiety as well as other emerging novel treatment methods. However, progress in research on MDD and GAD has been challenging due to high individual variability in symptoms and course, high levels of comorbidity with other psychopathology, and genetic *and* environmental influences. Given these challenges, identifying novel and personalized methods is crucial for advancements in research on depression and anxiety. The therapeutic link between MDD/GAD and gut microbiota is advantageous because of the greater accessibility and modifiability of the microbiome compared with the human genome [32]. Given the adaptable nature of the microbiome, it may be a good representation of the individual’s history and could explain the differences in risk of illness, disease course, and response to treatment. If MET-2 alleviates symptoms of neuropsychiatric disorders, they could be offered to patients as personalized, alternative, and/or adjunctive treatments to combat specific symptoms that tie together specific gut bacteria strains or the gut as a whole to the brain.

However, possible limitations of this trial include difficulty recruiting individuals with depression or anxiety that are not currently on any antidepressant medication or due to stigma associated with fecal and/or natural products. Compliance with the treatment schedule can also be more difficult for individuals with mental illness [33]. These issues will be minimized by widespread advertising and a detailed explanation of study requirements before signing the informed consent form. Participants will also be asked to keep a mood and symptom chart where they will also track their investigational product use. A researcher from the study team will discuss the details of the chart at each in-hospital visit to assess potential adverse symptoms and maintain a record of investigational product compliance. Given that this is an open-label trial, other limitations include small sample size, lack of a placebo arm, and a short follow-up period.

In summary, to our knowledge, this will be the first study to show evidence for the role of microbial therapy in treating depression and anxiety. Furthermore, the results of the trial will contribute to a growing body of research on assessing gut repopulation as a potential treatment method for MDD and GAD and could further explain the relationship between the gut and the brain and the underlying mechanisms.

## Appendix

Multimedia Appendix 1 Peer-reviewer report from MITACS.

## Abbreviations

5-HT: serotonin
AEs: adverse events
ANOVA: analysis of variance
CFU: colony-forming unit
CNS: central nervous system
DA: dopamine
FMT: fecal microbiota transplantation
GAD: generalized anxiety disorder
GCP: good clinical practice
GI: gastrointestinal
GSRS: gastrointestinal symptom rating scale
HPA: hypothalamic-pituitary-adrenal
HSREB: Health Sciences and Affiliated Teaching Hospitals research ethics board
ICH: International Council for Harmonisation of Technical Requirements for Pharmaceuticals for Human Use
IgA: immunoglobulin A
IgM: immunoglobulin M
IL-10: interleukin 10
IL-6: interleukin 6
MADRS: Montgomery-Asberg Depression Rating Scale
MDD: major depressive disorder
MET-2: microbial ecosystem therapeutic-2
MINI: mini-international neuropsychiatric interview
NE: norepinephrine
SAEs: serious adverse events
TGF-β: transforming growth factor beta
TNF-α: tumor necrosis factor alpha
TSES: Toronto side effects scale
